## RATIONALE

Patients and survivors of breast cancer present impaired physical fitness and various complications including acute and chronic pain, severe fatigue, limited range of motion, and bone loss attributable to anticancer treatments. Therefore, regular exercise during and following cancer treatments has been recommended to enhance physical capabilities and relieve severity of side effects, leading to an improved quality of life. Although the clinical utility of exercise-oncology has consistently emerged as a critical component of lifestyle modification to improve survival and reduce risk of recurrence, there is less evidence relating exercise to tumorigenesis-related factors and the biologic mechanisms underlying this association remain unclear. Despite the general benefits known to patients with cancer, the effects of exercise on the initiation and progression of the tumor itself remain unclear.

Wingless and integration site growth factor (Wnt) signaling plays vital roles in numerous cellular processes, including development, differentiation, proliferation, apoptosis, cell motility, and maintenance of the stem cell niche. For instance, Wnt signaling is crucial for breast development during pregnancy and lactation. Despite its physiologic importance, abnormal Wnt signaling is one of the major tumorigenesis-related signaling pathways. Particularly, aberrant Wnt signaling is closely linked to tumorigenesis such as the development of breast cancer. Therefore, Wnt-signaling molecules and their regulatory factors are potential biomarkers for cancer diagnosis as well as therapeutic targets.

Under oncogenic stress, Wnt signaling is triggered and  $\beta$ -catenin accumulates in the cytosol due to inhibition of ubiquitin-proteasomal degradation. The cytosolic  $\beta$ -catenin translocates into the nucleus, binds with T cell factor/lymphoid (TCF) enhancer factor and acts as a transcriptional cofactor. This complex induces a variety of downstream target genes, including Wnt-induced secreted protein 1 (WISP-1). WISP-1 expression is observed during organ development, wound healing, and tissue repair. However, WISP-1 expression is abnormally increased in pathologic conditions such as fibrosis and cancers. Recently, an in vitro and in vivo study has demonstrated that WISP-1 not only promotes growth of human breast cancer cells by downregulating tumor suppressor genes and cell-cycle inhibitors, but it also encourages metastatic potential by stimulating epithelial to mesenchymal transition traits. Thus, WISP-1 is a potential therapeutic target as an independent tumorigenic risk factor for human breast cancer.

On the other hand, it has been suggested that WISP-1 is a novel adipokine associated with obesity, hypertriglyceridemia, hyperleptinemia, insulin resistance and adipose tissue inflammation. Notably, as a consequence, glycogen synthesis is reduced in myotube, and gluconeogenic genes are upregulated in hepatocytes. Given that metabolic disturbances are risk factors for cancer development and poor prognosis, WISP-1 is a candidate pathologic biomarker reflecting both systemic metabolic deterioration and cancer prognosis. Furthermore, therapeutic strategies targeting recovery of circulating Wnt-related protein levels are worthwhile to explore for the management of metabolic risk factors in cancer patients.

[figure not shown]

## OBJECTIVES

We hypothesize that regular exercise could be an effective strategy to reduce expression of Wnt signaling molecules in breast cancer survivors. The primary aim of this study is to compare the changes in serum WISP-1 and  $\beta$ -catenin levels elicited by exercise intervention. As a preliminary observation to this, an age-matched comparison in those baseline levels between cancer survivors and healthy persons will be conducted. As secondary aims, we will assess the effects of the intervention on kinanthropometric (body composition and physical fitness) parameters and blood gluco-lipid metabolic profile and analyze their relationship with Wnt signaling indicators.

## METHODOLOGY

### *Study design*

**Randomization** The Lifestyles Of Health And Sustainability for Breast Cancer Survivors (LOHAS-BCS) is a single-center, two-armed randomized controlled trial. Eligible participants are randomly assigned to either an exercise intervention group or a control group using sealed, computer generated random numbers with the allocation ratio of 1 to 1.

**Study procedures** Demographic characteristics are collected from personal interviews and self-reported surveys. Clinical characteristics are obtained from electrical medical records. Measurements are conducted at baseline and 12-week intervention, which include anthropometry, body composition, health-related fitness levels, and blood sample collection.

**Blinding** Four research staff members who are unaware of group assignment performed all outcome assessments. The statistician is unaware of treatment allocation until completion of the statistical analyses. Participants are not blind to their assignment but are unaware of main outcome measures, and are instructed to avoid mentioning anything regarding their study experience to the assessors.

### *Study participants*

Survivors of breast cancer, who visited the hemato-oncology center of Wonju Severance Christian Hospital, are recruited between June 2014 and December 2016. Treatment history and menstrual status are obtained from the clinical reports of the hemato-oncology center with the consent of participants. Written informed consent will be obtained from all participants included in the study. They are eligible to participate in this study if they met the following inclusion criteria without exclusion criteria, with medical clearance from their oncologist.

[figure not shown]

1. **Inclusion Criteria:**

- 1) Have diagnosed as a stage of I-III breast cancer
- 2) Have undergone lumpectomy or mastectomy
- 3) Have completed neoadjuvant/adjuvant chemotherapy and able to initiate Exercise program
- 4) Nonsmokers (i.e., not smoking during previous 12 months)
- 5) Able to provide physician clearance to participate in exercise program for 12 weeks

2. **Exclusion Criteria:**

- 1) History of chronic disease including diabetes, uncontrolled hypertension or thyroid disease
- 2) Weight reduction  $\geq 10\%$  within past 6 months
- 3) Metastatic disease
- 4) Participate more than 60 minutes of exercise per week in the past 6 months
- 5) Cardiovascular, respiratory or musculoskeletal disease or joint problems that preclude moderate physical activity

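### Entry sets no interval since surgery or chemotherapy, so any natural WISP-1 change would count as an exercise effect in the planned before-after tests; comparing the arms removes it in expectation and leaves a precision cost

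*Protocol*

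**What the plan says.** Under Study participants (and again in the Study Protocol Summary), the two inclusion criteria that bear on treatment timing are "Have undergone lumpectomy or mastectomy" and "Have completed neoadjuvant/adjuvant chemotherapy and able to initiate Exercise program". Neither carries a minimum or maximum interval. Women also enter "with medical clearance from their oncologist", which is a safety check and not a time window.

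The Rationale states that "WISP-1 expression is observed during organ development, wound healing, and tissue repair". It also opens by describing impaired fitness in these women, together with complications such as "bone loss attributable to anticancer treatments".

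Under Objectives, "The primary aim of this study is to compare the changes in serum WISP-1 and" beta-catenin brought about by exercise. Allocation is made "using sealed, computer generated random numbers with the allocation ratio of 1 to 1", and no stratification factor is named. The control arm is measured at the same two times, baseline and 12 weeks, and is told to keep to its usual activity.

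The Data analysis section, like the Summary, names a paired t-test or Wilcoxon signed-rank test of values before and after training for fitness, body composition and serum biomarkers. It names no test between the arms. Time since treatment has no stated role, although "Treatment history and menstrual status are obtained from the clinical reports of the hemato-oncology center".

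**The concern.** A woman whose operation followed neoadjuvant chemotherapy can qualify soon after surgery, while another may be years past treatment. By the protocol's own account the main marker is active in tissue repair, so the first woman's WISP-1 could move over 12 weeks for reasons unrelated to exercise, and the second woman's need not. Fitness reduced by treatment might also recover with time.

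Two things are at stake. First, a paired test in the exercise arm cannot separate natural change from the effect of training. Second, even when the arms are compared, a mixture of changing and stable women widens the spread of the 12-week change, and at 17 to 25 per arm the two kinds of women may be split unevenly by chance.

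**Working it through.** **Inputs from the protocol (Sample size).** Mean 2,104 and SD 472 pg/mL; target difference 25%, so 0.25 × 2,104 = 526 pg/mL; two-sided alpha 0.05; power 90%; 17 per arm, raised to 25 for about 30% dropout.

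**The plan's own figure.** n = 2 × 472² × (1.96 + 1.28)² / 526² = 16.9, so 17 per arm; 17 / 0.70 = 24.3, so 25. Both reproduce and neither is in dispute.

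**Assumed inputs, because the documents give none.** A share p of 30% to 50% of women are recently treated; their WISP-1 falls by 15% to 25% without exercise, that is d = 0.15 × 2,104 = 316 to 0.25 × 2,104 = 526 pg/mL; the pre-post correlation is 0.5. The SD of change without any mixture is then 472 × √(2 × (1 − 0.5)) = 472.

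**Step 1: the paired test within one arm, with no exercise effect.** The arm mean shifts by p × d: 0.3 × 316 = 95 to 0.5 × 526 = 263 pg/mL, or 18% to 50% of 526. For n = 17 and SD of change 472, the noncentral t distribution gives rejection in about 12% to 58% of trials. Allowing for the extra variance of the mixture (step 2), the upper figure is about 47%.

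**Step 2: the between-arm comparison of change.** The expected shift is the same in both arms and cancels. In a simulation with half the women falling by 10%, 25% or 50%, type I error at 17 per arm stayed at about 5%. The cost is in variance: SD of change = √(472² + p(1 − p)d²).

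| Assumption | SD of change (pg/mL) | Power for 526, 17 per arm | Power for 526, 25 per arm |
|---|---|---|---|
| No natural change | 472 | 88% | 97% |
| 30% of women fall 15% | √(472² + 0.21 × 316²) = 494 | 85% | 96% |
| 50% of women fall 25% | √(472² + 0.25 × 526²) = 540 | 79% | 92% |

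The 88% in the first row is the t-based value; the protocol's normal approximation gives 90%.

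**Step 3: chance imbalance.** With unstratified 1:1 allocation, binomial counts give a difference of at least 20 percentage points in the recently treated share in 16% (p = 0.3) to 20% (p = 0.5) of trials at 25 per arm, and in 19% to 23% at 17 per arm. These figures count both directions, so about half of such trials would favour exercise. A 20-point imbalance moves the contrast by 0.20 × 316 = 63 to 0.20 × 526 = 105 pg/mL, which is 12% to 20% of 526.

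**The case against.** The strongest reply is that the trial already has the remedy for natural recovery: a concurrent randomised control arm. Recovery is equal in expectation in the two arms, so the entry criterion does not mix it with the exercise effect. The mixing comes from the paired tests. Any drift would produce it, and a narrower entry window would not cure a missing between-arm test. This stands.

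A reader might also infer that chance imbalance biases the between-arm contrast. It does not on average. It is random error that the standard error already carries, and it matters only for the particular allocation obtained. A reader might further infer that WISP-1 is bound to fall in the hypothesised direction. The Rationale says only that expression is seen in repair. It says nothing about serum levels weeks or months after breast surgery, so the shares and falls used above are illustrations. Being able to start exercise, together with oncologist clearance, also makes entry during acute healing less likely, although neither fixes a time.

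Finally, broad entry is a legitimate choice for a single-centre trial of 50 women, and covariates are often left to a statistical analysis plan, which is not shown here. That is fair as far as the missing covariate goes. It does not answer the fact that the protocol itself specifies before-after tests for its primary markers.

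**Conclusion.** The point holds in a limited form. The protocol leaves the interval since treatment open while naming tissue repair as a source of its main marker, and under the tests it specifies any natural change would be credited to training. The false-positive range of 12% to 58% (47% at the top once mixture variance is counted) belongs to the paired test, not to the eligibility criterion. With the arms compared, type I error stays near 5%. What remains is a modest loss of power (about 3 to 9 percentage points at 17 per arm and 1 to 5 at 25) and a possible shift of 63 to 105 pg/mL under a 20-point imbalance. All of these sizes rest on the assumed shares, falls and correlation. If natural change is absent, the cost is nil. The documents do not support the stronger conclusion that open entry by itself invalidates the randomised comparison.

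**What to change.** Analyse 12-week WISP-1, beta-catenin and the fitness measures between arms by ANCOVA, adjusted for the baseline value and for one prespecified time-since-treatment covariate, for example log months since the last surgery or chemotherapy. Take it from the treatment history already collected, and tabulate it by arm. The between-arm comparison removes natural recovery in expectation. The covariate then recovers precision and corrects a realised imbalance, to the extent that natural change follows time since treatment.

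The covariate costs one degree of freedom and no new data. A minimum entry interval is not required; it would trade recruitment for homogeneity. Stratifying randomisation by time since treatment is useful only if enrolment is still open, and the protocol dates recruitment from June 2014 to December 2016.

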**Interventions**

**Exercise group** The exercise training program is designed following the American College of Sports Medicine cancer guidelines (exercise intensity, frequency, time, and type), and are performed at least three times per week for total 12 weeks, under the direct supervision of exercise physiologists. Exercise training is conducted with individual's ratings of perceived exertion intensities within 11–13 that are gradually and moderately increased at 4-week intervals until reaching a rating of 13–15. Each session begins with a warm-up consisting whole body stretching and flexibility exercises for shoulder muscles stiffness such as finger climbing, shoulder glides (inferior, anterior, and posterior), and pendulum exercises for 10 min. The exercise program incorporates step aerobics on 17-cm (6.7-inch) platforms for 20 min followed by the strength training using body weight consisting of shoulder press, black burn exercise, wall push-up, biceps curl-up, plank exercise, leg bridge, squat, and calf raise for 20 min. At the end of the session, subjects perform cool-down involving easy walking and stretching exercises for 10 min (Table 1). Subjects in the exercise group are encouraged to participate in a home-based exercise session at least 30 minutes once and more weekly for 12 weeks.

**Control group** Participants in the control group are instructed to maintain their routine physical activities and not to participate any new exercise programs during the 12-weeks study period. Afterwards, the subjects who complete both pre and post-test received an opportunity to participate in the same exercise program that the intervention group has performed.

**Table 1. Supervised and group-based exercise intervention program for 12-weeks**

| Contents             | Work out                                         | Frequency                                                                                                                                                                | Time                    | Intensity                                |
|----------------------|--------------------------------------------------|--------------------------------------------------------------------------------------------------------------------------------------------------------------------------|-------------------------|------------------------------------------|
| Warm-up       | Shoulder static stretching
Dynamic stretching |                                                                                                                                                                          | 10 min                  | RPE 10                                   |
| Main exercise | Step aerobics                                    | Step jacks / side jacks
March step/jacks
Step back + knee up
Side-to-side steps
Side leg swings
Cross step arm extension,
Alternating steps back, etc. | 10~20 rep.              | 20 min                                   |
|                      |                                                  |                                                                                                                                                                          |                         | 1 ~ 4 wks,
RPE 11~13                  |
|                      |                                                  |                                                                                                                                                                          |                         | 5 ~ 12 wks,
RPE 13~15                 |
|                      |                                                  |                                                                                                                                                                          |                         | 9 ~ 12 wks,
RPE 15                    |
|                      | Upper body                                       | Shoulder press
Arm/triceps curls                                                                                                                                      | 12~16 rep.
x 2~3 set | 20 min                                   |
|                      | Trunk/core                                       | Crunch
Plank
Bridge
Leg raise
Dead lift                                                                                                                      |                         | OMNI-Resistance
Exercise
Scale 6~8 |
|                      | Lower body                                       | Squat
Lunge
Hamstring, kickback                                                                                                                                    |                         |                                          |
| Cool-down     | Shoulder static stretching
Dynamic stretching |                                                                                                                                                                          | 10 min                  | RPE 10                                   |

RPE, ratings of perceived exertion

### **Observations**

**Primary outcomes** The aim of the study is to assess and understand the effects of an exercise program on health-related physical fitness and biomarkers involving cancer-related molecules. For this reasons we will evaluate:

1. Changes of cancer-related biomarkers such as serum levels of Wnt1-inducible signaling pathway protein-1 (WISP-1) and its upstream  $\beta$ -catenin.
2. Components of health-related physical fitness including cardiorespiratory fitness, muscular exercise capacity and flexibility.
3. Risk parameters of metabolic diseases including anthropometric and body composition variables, and blood gluco-lipid profiles.

### **Outcome measures**

1. Wnt signaling-related biomarkers

Blood samples are drawn from the antecubital vein and collected in serum separation tubes. The tubes are centrifuged at 3000 rpm (1,000  $\times$ g) for 10 min, and serum samples are collected and immediately stored at -80°C until analysis. Commercially available enzyme-linked immune sorbent assay (ELISA) kits are used to measure the changes of serum levels of Wnt signaling-related molecules such as WISP-1 and

[figure not shown]

$\beta$ -catenin according to the manufacturer's protocol.

1) WISP-1

- Product code, SCG895Hu
- Manufacturer, USCN Life Science Inc.
- Minimal detectable density (sensitivity), 0.97 pg/mL
- Standard curve range, 2.74 - 2,000 pg/mL
- Intra-assay, CV<10%; inter-assay, CV<12%
- Test method: double-antibody sandwich; detection wavelength, 450 nm

2)  $\beta$ -catenin

- Product code, CSB-E08963h
- Manufacturer, CUSABIO Technology
- Minimal detectable density (sensitivity), 3.9pg/mL
- Standard curve range, 15.6 - 1,000 pg/ml
- Intra-assay, CV<8%; inter-assay, CV<10%
- Test method: double-antibody sandwich; detection wavelength, 450 nm

2. Health-related physical fitness

- 1) Muscular strength is assessed by the maximum voluntary strength of handgrip (kg). Grip strength is measured 4 times, twice each of the dominant and non-dominant hands, and the mean and maximum values is recorded to the nearest 0.1 kg (TKK-5401, Takei, Japan).
- 2) Muscular endurance is assessed using sit-up test. The maximum repetitions for 30 seconds are recorded. To assure the starting position, the participants lie on their back with knees flexed, feet on the floor with hands on the opposite shoulders. Arm contact with the chest must be maintained. The chin should remain tucked on the chest. The sit-ups are completed when the elbows touch the thighs. To complete the sit-up, the participants returns to the down position until the mid-back makes contact with the testing surface (BS-SU, InBody Co., Korea).
- 3) Muscular power is assessed using standing long jump test. The maximum horizontal distance of two trials is recorded to the nearest 1 centimeter.
- 4) Aerobic capacity is assessed using Progressive Aerobic Cardiovascular Endurance Run (multi-stage

20-meters PACER test). Participants are instructed to run back and forth between two lines, 20-meters apart for the time allowed at the sound of a tape-recorded beep. The test score is recorded as the number of shuttles completed on pace, and only one trial is permitted. Before the actual test, all participants perform a short pilot trial run to help them understand how to pace themselves. During the test, all participants are encouraged with positive feedback such as “good job”, “keep it going” etc. When the participants are unable to make it to the marks on two consecutive beeps, the test are terminated and instructed to walk around to cool-down.

- 5) Agility is assessed using 10-meters agility shuttle run test. Two parallel lines were drawn on the floor 10 m apart. Participants run twice back and forth as fast as possible, covering a total distance of 20 m, while picking up a designated piece of wood placed at the furthest point. Time recording is stopped when the participants crossed the end line with one foot. The lower value of two trials is recorded to the nearest 0.01 second.
- 6) Flexibility is assessed using sit and reach test with a flexometer (BS-FF, InBody Co., Korea). The test is performed by sitting with the feet barefoot straight against the vertical plane of the measuring instrument. Then with both hands gathered and knees fully upright, the upper body bends forward and pushes the meter as far forward as possible. The point where the fingertip stops at about 2 seconds was measured and the high value was recorded to the nearest 0.1 centimeter.

